### Sample size calculation

A pilot study was conducted to guide the design of this research. Based on the pilot data, we plan to recruit up to 20 participants per group, accounting for an estimated 20% attrition rate [40], to ensure at least 15 participants with complete data to be included in the analyses for sufficient statistical power (β ≥ 80%, α = 0.05). This sample size is calculated based on using a two-sample two-sided t-test to detect significant differences between the SCI and control groups for the change from baseline in ANS-CV function. High-frequency heart rate variability (HF HRV) reflects parasympathetic activity, with normalized units accounting for changes in total power during autonomic activation [41–43]. Similarly, low-frequency systolic blood pressure variability (LF SBPV; Mayer waves) serves as a biomarker of sympathetic vasomotor control [44]. Based on the pilot study, the estimated minimum detectable effect sizes are 24.97 for the difference in normalized HF HRV and 3.52 mmHg² for the difference in LF SBPV between groups, which are the two primary ANS-CV variables.

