### Data analysis

To analyze the impact of HIIE on cardiovascular, cerebrovascular, and cognitive functions in individuals with SCI compared to controls, linear mixed-effects models (LMMs) will be utilized. These models will assess the main effects and interactions of group (SCI vs. controls) and time (pre-HIIE vs. post-HIIE) across different outcomes, with specific adjustments tailored to the type of function being analyzed. The general model can be structured as follows:

Y_ij_ = β_0 _+ b_i_ + β_1_Group_i_ + β_2_Time_j _+ β_3_Group_i _× Time_j _+ β4 × Covariates_i _+ ∊_ij_

Where:

Y_ij_ represents the dependent variable (e.g., HR, BP, HF HRV, LF SBPV, BRS) for subject *i* at time j (j = 0,1).Group_i_ is the SCI/control status for subject *i* (SCI: Group_i _= 1, Control: Group_i_ = 0).Time_j_ is the *jth* time point (pre-HIIE: Time_j_ = 0, post-HIIE: Time_j_ = 1).Covariates_i_ are additional covariate(s) for subject *i*. For dependent variables within cardiovascular and cerebrovascular functions: baseline physical activity levels. For cognitive function: pre-morbid intelligence and psychological distress.b_i_ is the random effect for subject *i* to account for within-subject correlation over time and is assumed independent N(0, σ_b_^2^).∊_ij_ is the residual error term assumed independent N(0, σ_∊_^2^).

Estimation of parameters will be analyzed by restricted maximum likelihood estimation (REML). Wald tests will be used to assess the significance of the predictors, with the significance level set at p < 0.05. All analyses will be conducted using RStudio (© 2009–2024 Posit Software, PBC).

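### The mixed-model tests are called only Wald tests, with no finite-sample reference, although the trial was sized on a t-test; on the usual normal or chi-square reading the 5% Group × Time test runs at about 6% with 15 per group.

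*Protocol article*

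**What the plan says.** The Data analysis section gives one general model for all outcomes: a random intercept per participant, fixed effects for group, time (pre or post) and their interaction, and one or two participant-level covariates. Estimation is by REML. On testing it says: "Wald tests will be used to assess the significance of the predictors, with the significance level set at p < 0.05". On software it says only: "All analyses will be conducted using RStudio". No package, reference distribution, denominator degrees of freedom or small-sample correction is named, and confidence intervals are not mentioned.

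The Sample size calculation section takes a different reference: "This sample size is calculated based on using a two-sample two-sided t-test", applied to the difference between groups in change from baseline. The recruitment target is set "to ensure at least 15 participants with complete data to be included in the analyses", at 80% power and a 5% significance level.

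**The concern.** With two time points and complete data, the Group × Time coefficient in this model is the difference between groups in mean change. That is the contrast the t-test was used to size. A Wald statistic referred to a normal or chi-square distribution treats the estimated variance as if it were known. With 30 participants it is not: the contrast has 28 error degrees of freedom. On that reading, sizing and analysis use different reference distributions for the same quantity, and the test rejects a true null more often than the stated 5%.

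A second effect can add to this. The random-intercept variance cannot be negative. When the data suggest a negative pre-post correlation, REML sets the variance to zero, pools the two error sources and understates the standard error of change. This matters only if the true correlation is low.

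The same test serves every primary and secondary outcome, so the stated level would be slightly wrong throughout.

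**Working it through.** **Inputs from the protocol article.** At least 15 complete participants per group, up to 20 recruited, 20% attrition, 80% power, two-sided 5%, two-sample t-test (Sample size calculation). Random intercept, two time points, REML, Wald tests at p < 0.05 (Data analysis). No SD and no pre-post correlation is given.

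**The plan's own figures.** 15 / (1 − 0.20) = 18.75, so 19 recruits per group would be enough. The plan says up to 20, and 20 × 0.80 = 16, so this is consistent. The 15 itself cannot be recomputed without an SD. Working backwards, a two-sided t-test with 15 per group and 80% power detects a standardized difference of d = 1.06. The plan states: "the estimated minimum detectable effect sizes are 24.97 for the difference in normalized HF HRV and 3.52 mmHg² for the difference in LF SBPV". These imply change-score SDs of about 24.97 / 1.06 = 23.6 and 3.52 / 1.06 = 3.32 mmHg².

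**True level with a normal reference.** Under the model the Group × Time statistic follows a t distribution on 2n − 2 degrees of freedom, so the level is 2 × P(t > 1.960):

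| Analysed per group | df | True level |
|---|---|---|
| 20 | 38 | 5.7% |
| 16 | 30 | 5.9% |
| 15 | 28 | 6.0% |
| 10 (assumed) | 18 | 6.6% |

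Terms tested between participants have 27 degrees of freedom with one covariate and 26 with two, giving 6.0% and 6.1%. The 10-per-group row is a scenario. The Limitations section reports that the MCA could not be found at the later session in two of six participants of an unpublished study. Losing one third of 15 leaves 10.

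**Interval width.** The t quantile on 28 degrees of freedom is 2.048. A normal-based interval has relative width 1.960 / 2.048 = 0.957, which is about 4% too narrow, with 94.0% coverage.

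**Power.** At d = 1.06 and 15 per group, power is 82% with the 1.960 cut-off and 80% with 2.048. Only the t cut-off returns the power the plan claims.

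**Zero-variance boundary.** REML random-intercept model, one covariate, 15 per group, 1,000,000 simulated trials per setting. The correlations are assumed:

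| Pre-post correlation | Variance set to zero | Level, normal cut-off | Level, t cut-off (28 df) |
|---|---|---|---|
| 0 | 50% | 6.7% | 5.6% |
| 0.2 | 15% | 6.1% | 5.1% |
| 0.5 | 0.3% | 6.0% | 5.0% |
| 0.8 | 0% | 6.0% | 5.0% |

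At a correlation of 0.2 or more, the boundary adds at most about 0.1 percentage point. Only near zero does it add materially, and there the t cut-off alone does not fully restore 5%.

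**The case against.** The strongest reply is that the text never says large-sample. A Wald statistic can also be referred to a t or F distribution with finite degrees of freedom, and some R routines do so by default. On that reading the Group × Time test is already at 5% and agrees with the sizing exactly. This stands as a limit on the claim: the inflation is conditional on the normal or chi-square reading, which is the ordinary meaning of an unqualified Wald test but is not stated.

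A related reply is that degrees-of-freedom methods are usually left to a statistical analysis plan. That would dispose of a pure omission. Here, however, the article does fix the model, estimator, test and level, and the test as worded does not match the t-test used for sizing. The remedy is a better-suited test, not just a missing detail.

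A reader might infer that the tests run at 6% to 7% at the planned sample size. The documents do not support the upper end. At 15 per group 6.7% needs a correlation of zero, which is hard to expect in measurements on the same person at one visit, and 7% or more also needs fewer than 15 per group. The documents give neither condition. Since 15 is the planned minimum, 6.0% is about the worst case under ordinary correlation.

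A reader might also infer that the planned confidence intervals are too narrow. The article plans none, so that part applies only to intervals that may be reported later.

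**Conclusion.** The point holds in a limited form. The Data analysis section leaves the reference distribution of its Wald tests open, while the Sample size calculation section relies on a t-test for the same contrast. On the usual normal or chi-square reading, the Group × Time test has a true level of about 6.0% at 15 per group, an excess of one percentage point. It would be about 6.6% if usable data fell to 10 per group, and about 6.7% at 15 per group if the pre-post correlation were near zero; both are assumptions. These figures also rest on the model's normality and equal-variance assumptions.

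The sample size is not affected, and only results close to p = 0.05 could change. The documents do not support saying that every p-value is anti-conservative, because a t or F reading is possible. The correction is still worth making, because it removes the ambiguity at almost no cost.

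**What to change.** In the Data analysis section, replace Wald tests with t or F tests on Kenward-Roger or Satterthwaite degrees of freedom, at the two-sided 5% level, and add that any confidence intervals reported will use the matching t quantiles. If a t or F version was always intended, the same sentence says so.

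As an optional safeguard, analyse change scores or use an unstructured 2 × 2 within-participant covariance, so that a variance held at zero cannot understate the standard error of change. This matters only if the pre-post correlation turns out to be near zero.

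The cost is one sentence and slightly larger p-values: the cut-off at 15 per group moves from 1.960 to 2.048. No extra participants are needed, and power at the stated detectable differences stays at the claimed 80%.

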### Data management

The investigators will implement measures to ensure participant anonymity by utilizing deidentified data. The identification key linking participants to their study identifiers will be securely maintained and accessible only to authorized study personnel. The data will be overseen by the University IRB. All signed informed consent forms will be retained for the IRB-mandated period of three years following the conclusion of the study. Any adverse events reported during the intervention will be promptly communicated to the University IRB.

### Study status

The initial IRB approval (Version 1) date was January 28, 2024. Study recruitment began on February 14, 2024, with an anticipated completion date of May 30, 2025. Data collection is currently ongoing.

### Data

Deidentified data will be made available upon reasonable request to the Principal Investigator (PI) and solely for scientific review purposes. Access to the data will be granted only after the results have been published in peer-reviewed journals.

## Discussion

High-intensity interval exercise (HIIE) as a therapeutic intervention for individuals with SCI has emerged as a promising area of research [35], particularly in its potential to address disruptions in ANS function [12,26]. While broader benefits of exercise for cardiovascular and cerebrovascular health are well-documented in the non-injured population [82,83], its specific effects on individuals with SCI, particularly those with a NLI at or above T6, remains poorly understood. Current evidence lacks normative values for ANS-CV and cerebrovascular parameters in SCI. While LF SBPV less than 2 mmHg^2^ predicts OH [44] and higher diastolic CBFV correlates with better cognitive performance [84], absolute thresholds defining ANS-CV or cerebrovascular dysfunction remain undefined for this population. While this acute cross-sectional study cannot determine definitive efficacy endpoints or minimum clinically important differences (MCIDs) for HIIE in SCI, the findings will identify acute physiological responses that may predict clinically meaningful outcomes. In particular, we will evaluate pre- to post-HIIE changes in the ANS-CV, cerebrovascular, and cognitive variables between the SCI and control groups. If the direction and pattern of post-HIIE responses in the SCI group resemble those observed in the control group, this may be indicative of adaptive or beneficial changes, even if absolute response magnitudes are blunted. Additionally, the outcome measures obtained from the control group may provide preliminary normative data to inform future investigations in this field. This is particularly relevant given the unique challenges faced for people with SCI, including impaired BP and HR regulation, and decreased cognitive performance, all of which can profoundly impact quality of life [13].

Previous studies have highlighted the benefits of long-term exercise regimens on ANS and cognitive function in individuals with SCI, possibly through ventricular remodeling, enhanced myocardial contractility, improved BRS, improved respiratory function, and increased CBF [12,21,24,28,30,82,85]. Additionally, the potential benefits of exercise on ANS-CV function in individuals with SCI may be mediated by non-neuronal mechanisms, such as increased circulating catecholamines that enhance cardiovascular responses to exercise, despite impaired sympathetic innervation to the heart [86]. An exaggerated chemoreflex sensitivity, commonly observed in SCI, may also contribute to these effects [87], along with residual pressor responses to exercise, particularly in those with higher-level injuries [88]. Together, these compensatory pathways may help explain observed improvements in ANS-CV function following exercise, even in the presence of disrupted descending sympathetic control. The current investigations on ANS-CV, cerebrovascular, and cognitive functions in SCI primarily focused on moderate-intensity or long-duration interventions, leaving a critical gap in understanding the impact of intensity-focused, time-efficient protocols such as HIIE, especially since lack of time is a significant barrier to physical activity among individuals with SCI [89]. Acute HIIE has been shown to improve wall shear stress and endothelial function in obese or sedentary individuals [90,91], which may subsequently benefit ANS-CV, cerebrovascular, and cognitive functions, though these mechanisms require further investigation in people with SCI [92–94]. Moreover, existing research has often generalized findings across participants with varying NLIs, limiting the applicability of results to individuals with more severe cardiovascular dysfunction associated with higher-level injuries [12,21,24,28,30].

This study protocol addresses these gaps by focusing on the acute effects of HIIE, a short-duration yet high-impact exercise modality, on ANS-CV, cerebrovascular, and cognitive outcomes in individuals with SCI at or above T6. Unlike previous exercise studies in SCI [12,21,22], this protocol incorporates sensitive ANS-CV tests, such as the SUT and FCT, rather than relying solely on resting conditions. This approach provides a more dynamic and comprehensive understanding of how HIIE influences physiological and cognitive functions in this population. Furthermore, this study incorporates critical covariates (i.e., physical activity levels, pre-morbid intelligence, and psychological distress) to ensure robust and nuanced analyses. By addressing these variables, the study aims to generate findings that are both clinically relevant and generalizable. This approach is particularly innovative, as previous studies have largely overlooked the interplay between these covariates and exercise-induced physiological changes in the SCI population.

The implications of this research extend beyond the immediate outcomes. By demonstrating the feasibility and potential benefits of HIIE, this protocol sets the stage for larger, long-term studies that aim to refine exercise prescriptions for individuals with SCI. Additionally, the use of advanced physiological monitoring techniques could pave the way for more personalized exercise interventions tailored to the unique needs of each individual, based on their ANS-CV, cerebrovascular, and cognitive profiles.

### Limitations

There are several inherent limitations in the study protocol. First, the research will utilize TCD to quantify CBFV. Notably, challenges in TCD data acquisition have been documented among certain demographics, including blacks, Asians, and elderly women, primarily due to a 10–15% prevalence of an inadequate acoustic window [40]. In our previous study (not published), despite performing TCD screenings at the consent stage to ensure the detectability of cerebral vessels, the MCAs were still not detectable in two of the six participants during subsequent experimental sessions. To mitigate this, photographic documentation of each participant’s MCA/PCA location will be captured during initial screenings. This strategy aims to expedite and ensure accurate MCA/PCA localization in subsequent experimental sessions. Second, participants will provide self-reported information regarding their NLI. It is important to acknowledge that this approach may introduce the possibility of inaccuracies arising from potential memory lapses and changes in NLI due to natural recovery affecting motor and sensory functions. To mitigate this limitation, the study will exclusively enroll individuals with chronic injuries, defined as those with an onset of injury exceeding 6 months. Previous evidence has indicated that NLI tends to stabilize after this period following the initial injury [95]. Third, it’s pertinent to highlight that the scope of this study is restricted to particular parameters, excluding potential influences such as partial pressure of carbon dioxide level [96], sleep-disordered breathing [97], concurrent mild traumatic brain injury [3], or specific dietary impacts [98]. Subsequent research studies should consider these aspects to provide holistic insight into cognitive function post-SCI and the impact of exercise training. Fourth, due to the inconsistencies in current evidence regarding menstrual cycle effects on autonomic and cardiovascular responses [99,100], our study does not control for cycle phase. We recommend future research record basic menstrual cycle information (e.g., self-reported phase) to help contextualize individual response variability in training adaptations in females with SCI. Fifth, thermoregulatory compromise was not addressed in this study due to the brief duration of the HIIE protocol (10 minutes) and the controlled laboratory setting. However, we acknowledge that thermoregulatory challenges, particularly in individuals with NLI at or above T6, may compromise exercise responses in real-world applications. Future studies should standardize ambient temperature (20°C–25°C) and relative humidity (30%–50%) to mitigate such risks. Sixth, this protocol does not control for respiratory rate during the FCT, as common respiratory rate primarily affects HF HRV. However, previous evidence suggests that FCT induces minimal changes in respiratory rate [101]. Additionally, requiring participants to maintain a controlled respiratory rate could introduce unnecessary cognitive distraction, potentially affecting ANS function [102]. We therefore do not consider this a significant limitation of the study. Finally, this study does not assess post-exercise subjective fatigue. Although fatigue may influence cognitive performance during post-HIIE assessments, a validated fatigue scale (e.g., visual analog scale) was not included in the current protocol due to the timing of study initiation. Future studies should consider incorporating brief fatigue assessments to better differentiate cognitive effects that are exercise-induced versus those related to acute exertion.

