**Fig 2 pone.0326861.g002:**
[figure not shown]
Overview of the High-Intensity Interval Exercise Protocol. Notes: PPO, peak power output.

After a 5-minute recovery (for photoplethysmography re-instrumentation), assessments will proceed within the peak ANS-CV modulation window (10–30 min post-exercise) [65]. The order prioritizes transient ANS-CV effects first, followed by cerebrovascular and cognitive assessments (after 41 min total), as exercise-induced cognitive benefits persist longer than cardiovascular effects [66]. Alternate forms of the CVLT-III, SDMT, and COWAT will be used for post-HIIE assessments to avoid familiarization effects. Fig 3 outlines the planned testing procedures for V2 (Fig 3).

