### Outcome measures

**Primary outcome measures**: The outcome measures for our primary objective will include HF HRV, LF SBPV, BRS, HR, and BP during supine assessments, FCT, and SUT, both pre- and post-a single bout of HIIE.

**Secondary outcome measures**: The outcome measures for our secondary objective will include CBFV during cognitive testing and cognitive performance assessed pre- and post-a single bout of HIIE.

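### The reasons given for setting uncontrolled breathing aside do not cover the pre- versus post-HIIE comparison of HF HRV, or the supine and sit-up recordings

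*Protocol article*

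**What the plan says.** The sixth item under Limitations states that "this protocol does not control for respiratory rate during the FCT, as common respiratory rate primarily affects HF HRV". Two reasons follow for not treating this as a problem. One is that "previous evidence suggests that FCT induces minimal changes in respiratory rate". The other is that "requiring participants to maintain a controlled respiratory rate could introduce unnecessary cognitive distraction, potentially affecting ANS function". The paragraph concludes: "We therefore do not consider this a significant limitation of the study".

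Elsewhere in the article:

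- Outcome measures defines the primary outcomes as "HF HRV, LF SBPV, BRS, HR, and BP during supine assessments, FCT, and SUT, both pre- and post-a single bout of HIIE".
- Sample size calculation gives the physiological reading, "High-frequency heart rate variability (HF HRV) reflects parasympathetic activity", and names normalised HF HRV as one of two primary ANS-CV variables.
- Data analysis models each outcome on Group, Time (pre- or post-HIIE) and Group x Time. Baseline physical activity is the covariate for cardiovascular outcomes.
- Experimental procedure (text after Fig 2) times the post-exercise block: "After a 5-minute recovery (for photoplethysmography re-instrumentation), assessments will proceed".

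**The concern.** The evidence cited and the comparison tested are different contrasts. That face cooling hardly changes breathing is useful when a face-cooling (FCT) recording is compared with rest. The model contains no such term. It compares post-HIIE with pre-HIIE recordings, and compares that change between groups. Breathing may be the same during and before face cooling and still differ before and after exercise.

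The conclusion is also wider than its premises. The limitation is worded for the FCT, but it is dismissed for the study as a whole. HF HRV is equally a primary outcome in the supine and SUT recordings, for which no respiratory argument is offered.

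What is at stake is interpretation. If breathing differs after exercise while vagal activity does not, HF HRV moves and may be reported as a parasympathetic response to HIIE. If breathing recovers at different speeds in the two groups, the same can happen to the group difference. The article gives some ground for expecting differences: the Introduction notes impaired respiratory function in SCI, and the Discussion notes exaggerated chemoreflex sensitivity. Under Equipment, the BRS band is justified partly by its freedom from respiratory influence, so the authors apply this consideration to BRS but not to HF HRV across exercise.

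**Working it through.** **1. Which contrast each reason covers**

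| Reason in Limitations | What it bears on | Post vs pre HIIE? | Supine and SUT? |
|---|---|---|---|
| Face cooling hardly changes breathing | FCT vs rest | No | No |
| Paced breathing may distract | Whether to pace | No | No; it does not oppose measuring |

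**2. Timing of the post-HIIE recordings**

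Experimental procedure: 2 min warm-up + 3 x 20 s efforts + 2 x 120 s recoveries + 3 min cool-down = 2 + 1 + 4 + 3 = 10 min, which matches the stated 10 minutes. The Abstract starts post-exercise testing 5 min after the session, so the first recording begins about 3 + 5 = 8 min after the last effort. Taking the pre-HIIE order (15 min supine, 1 min FCT, 5 min recovery, 15 min SUT = 36 min), counted from the end of the session:

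- supine: 5-20 min
- FCT: 20-21 min
- SUT: 26-41 min

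This agrees with the Abstract's 36 and 41 minutes. The supine recording is the one nearest to exercise.

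**3. Which model terms are exposed**

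With SCI coded 1 and post coded 1, the change in controls is β2, the change in SCI is β2 + β3, and the group difference in change is β3. A breathing shift common to both groups enters β2 and β2 + β3 but cancels from β3. Only a differential shift reaches β3.

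**4. Change SD implied by the plan**

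Sample size calculation gives a detectable difference of 24.97 n.u. with 15 per group, 80% power, two-sided α 0.05 and a two-sample t-test, but no SD, so 24.97 cannot be reproduced independently. Solving the noncentral t (df 28) for 80% power gives a standardised difference of 1.060, so SD = 24.97 / 1.060 = 23.6 n.u.

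**5. Illustrative effect of a breathing shift**

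Assumptions: vagal activity unchanged, LF power fixed, baseline 30, 50 or 70 n.u., and HF power falling by 20% or 30% through breathing alone. None of these is in the documents.

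From Equipment, n.u. = 100 x HF / (HF + LF). At baseline 50 with a 20% fall: 100 x 40 / (40 + 50) = 44.4, a shift of 5.6. Let d = shift / 23.56. The rejection rate at nominal 5% comes from the noncentral t with df 28. The noncentrality is d√15 for the change within one group and d√7.5 for Group x Time when only one group shifts.

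| Baseline n.u. | Fall in HF | Shift, n.u. | d | Within group | Group x Time, one group shifts |
|---|---|---|---|---|---|
| 30 | 20% | 4.5 | 0.19 | 10.9% | 7.9% |
| 30 | 30% | 6.9 | 0.29 | 19.6% | 12.2% |
| 50 | 20% | 5.6 | 0.24 | 14.3% | 9.6% |
| 50 | 30% | 8.8 | 0.37 | 28.8% | 16.8% |
| 70 | 20% | 4.9 | 0.21 | 12.1% | 8.5% |
| 70 | 30% | 8.0 | 0.34 | 24.5% | 14.6% |

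If both groups shift by similar amounts, little reaches Group x Time. Falls of 30% and 20% from 50 n.u. differ by 8.8 - 5.6 = 3.3 n.u., and rejection is about 6.6%.

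**6. The HF band in breaths**

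0.15 x 60 = 9 and 0.45 x 60 = 27, so breathing slower than 9 or faster than 27 per minute puts the respiratory component outside the band.

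**The case against.** Several counter-arguments have force.

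- **The powered comparison is between groups.** A shift common to both groups cancels there, and the Introduction's remark on respiratory impairment concerns fitness benefits, not recovery of breathing after exercise. This stands. It limits the Group x Time problem to differential shifts but leaves the pre/post change in SCI, on which the primary aim rests, exposed.
- **The timing is not extreme.** All-out work totals 60 seconds, a 3-minute cool-down precedes the 5-minute recovery, and on the pre-HIIE order the FCT comes about 20 minutes after the session. Breathing may have settled by then. This stands for the FCT and SUT more than for the supine recording.
- **Pacing has a cost.** The distraction argument is a fair reason not to control breathing. It is no reason against estimating it.
- **A condensed article need not list every signal or sensitivity analysis.** Agreed. The absence of a respiration channel is not the point; the point is the reasoning the article does state.
- **Breathing is affected by exercise,** so adjusting for it changes what is estimated. This stands and limits what an adjusted model can be used for.

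A reader might infer that the plan tests a declared null of unchanged parasympathetic activity and that the test is therefore invalid. The documents do not support this. HF HRV itself is the named outcome and modelled variable, and the parasympathetic reading is an interpretation placed on it. A reader might also infer that false parasympathetic findings are likely. The documents give no breathing data, so that cannot be said either. A 50% fall in HF power from 50 n.u. would give 75% rejection within a group, but nothing in the documents supports a fall of that size.

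**Conclusion.** The stated rationale does not hold for the comparison the plan makes. Neither reason addresses a difference in breathing between pre- and post-HIIE recordings, and neither extends to the supine and SUT outcomes, so the dismissal for the whole study does not follow.

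The most exposed result is the pre/post change in HF HRV within the SCI group, chiefly supine. Over the 20-30% range examined, within-group rejection is about 11-29% against a nominal 5%. Group x Time rejection is about 8-17% if only one group shifts, and close to 5% if both shift alike.

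These figures rest on an SD back-solved from the plan's detectable difference, fixed LF power, and assumed baselines and falls in HF power. They show how sensitive the test would be, not what will happen. The matter is one of interpretation and is worth correcting; it does not invalidate the planned model.

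**What to change.** 1. Derive respiratory rate offline from the ECG already recorded, using R-wave amplitude modulation, for supine and SUT recordings pre- and post-HIIE, and for the FCT where quality allows. Do not use the HF peak of the R-R spectrum: it comes from the same spectrum as the outcome, and a peak sought within the band cannot reveal breathing outside it.
2. Report the pre-to-post change in respiratory rate by group, and flag recordings with breathing outside 0.15-0.45 Hz (9-27 breaths per minute).
3. Keep the planned HF HRV model as primary. Add one supportive sensitivity model with respiratory rate as a time-varying covariate. Use it to qualify the parasympathetic interpretation, not as a condition for reporting an effect, because respiratory rate is itself affected by exercise.
4. Replace the sentence dismissing the limitation with a statement that breathing after HIIE may influence HF HRV in all three recordings.

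Cost: modest offline processing and one additional model. No new procedure and no paced breathing are needed, and the work can be applied to data already collected. ECG-derived respiration is approximate and least reliable in the 1-minute FCT, so results for that recording need the most caution.
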